#### Data collection

Primary data will be collected using standardised questionnaires. We will use a novel approach of first engaging the participants in an in-depth qualitative interview with participatory data collection activities to facilitate them explaining their family, household, social and community circumstances. These in-depth qualitative data will facilitate the data collectors’ ability to confirm details, probe further and mitigate a bias toward the under-reporting of contacts. As part of the questionnaires, we will capture a single Global Positioning Satellite (GPS) coordinate for each participant’s home and other places in the community which will be identified as ‘shared spaces’ on electronic devices. We will record the coordinate of a participant’s home when the field team is at his/her home or at a community space. A separate enrolment form will be used to capture names and other identifying information. Data from the transmission hotspot identification study will be linked to electronic TB register data through personal identifying information such as name, surname and date of birth. A social network questionnaire will be used to identify shared socialisation settings, with GPS coordinates of these settings recorded.

#### Laboratory analyses

DNA will be isolated from sputum cultures at the NIP biosafety level 3 laboratory and the UNAM laboratory for samples with proven GeneXpert MTB/RIF rifampicin resistance and shipped to Research Center Borstel (RCB) for WGS. Isolated genomic DNA of individual strains will be sequenced using Illumina sequencing platforms and Nextera library preparation kits. All isolates will be sequenced with a minimum coverage of 50-fold. Raw read data (fastq files) will be mapped to the *M. tuberculosis* H37Rv genome (GenBank accession number NC_000962.3) using BWA-MEM, and mappings will be refined with the GATK software package. For variant (InDels and single nucleotide polymorphisms (SNPs)) detection in mapped reads, custom perl scripts will be employed with thresholds of a minimum coverage of four reads in both forward and reverse orientation, four reads calling the allele with at least a Phred score of 20 and 75% allele frequency. Multiple consecutive SNP calls (in a 12 bp window) that could indicate rare recombination sites or reflect artificial variant calls around InDels will be excluded. For alignment of a concatenated sequence for downstream analyses, variants in drug resistance-associated genes and repetitive regions will be excluded. Phylogenetic lineages (*M. tuberculosis* genotypes and known Beijing subgroups) will be inferred from specific SNPs.^7 8^ As proxy for TB cases associated with direct transmission events, a maximum pairwise genetic distance between at least two *M. tuberculosis* isolates of five SNPs will be used.^9^

#### Data management and analysis

Data will be captured into databases developed by a data specialist. WGS data will be analysed using a phylogenetic strain classification and a cluster/similarity analysis. Social network data will be analysed using thematic analysis for the description of typical and atypical social network contacts for people with MDR-TB in Namibia. Similarly, thematic analysis will be used for shared space data to identify the types of places where people with MDR-TB interact with other people to whom TB may be transmitted. Social network analysis, in conjunction with WGS cluster data, will indicate transmission hotspots within the regions. In our context, a hotspot is an area with a high TB incidence and where TB transmission happens, based on microbial genomic methods such as WGS and a collection of epidemiological approaches (social network and spatial analysis) and geographical map intersections between participants.

### Objective 2

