## Introduction

Namibia is classified by the WHO as a high tuberculosis (TB)-burden country and, in 2020, the TB incidence was estimated to be 460/100 000, with 12 000 new cases/year.^1^ The most recent nationwide anti-TB drug resistance survey in Namibia was completed in 2015, reporting a prevalence of multidrug-resistant (MDR)-TB at 4.5% among new cases and 7.9% among previously treated cases. Approximately 46.6% of patients with MDR-TB were coinfected with HIV.^2^ Based on that prevalence, the number of MDR-TB cases/year is estimated to be around 800. Only 213 cases were detected in 2020.

Namibia faces significant challenges at every step along the TB care cascade, from preventive therapy to diagnostics and patient treatment. Challenges also exist in the identification of prevalent cases of TB infection and disease through passive and active case finding intervention strategies.^3^ During the COVID-19 pandemic, Namibia observed an increased number of missed or undiagnosed TB cases with case management interruptions due to the diagnostic supply chain, redirections of resources and the effects of human movement restrictions, negatively impacting care-seeking.^4^

In the ‘hotspots, hospitals, and households’ (H3TB) study, we aim to identify MDR-TB transmission clusters, through genomic, geospatial and social data interferences, which could indicate transmission hotspots. We aim to determine the diagnostic yield of targeting these areas for active case finding as well as evaluating the cost-effectiveness of such approaches. Our central hypothesis is that geographical heterogeneity in the concentration of genotypes exists within the MDR-TB epidemic in Namibia leading to high-transmission areas (hotspots), where MDR-TB incidence could be up to three times that of the baseline population. Further, if these areas could be identified and targeted through enhanced case finding strategies, these strategies might be more effective than screening and treatment programmes which do not adapt to spatial and biological variation.^5^ In addition to targeting transmission hotspots, our focus will be on MDR-TB screening of household contacts of MDR-TB cases and visitors of hospitalised patients with MDR-TB.

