#### Participant identification

Individuals with a positive Xpert MTB/RIF result with rifampicin resistance demonstrated, and a positive *Mycobacterium tuberculosis* culture, will be included from the three regions. To identify transmission hotspots, whole genome sequencing (WGS) results will be combined with clinical, epidemiological, geospatial and social network data. A traditional sample size calculation is not indicated if most of the MDR-TB cases in a region are included (>80%).^5 6^ In this study, we might miss some MDR-TB cases who are not reported or diagnosed. However, a current surveillance study which started in January 2020 and is ongoing could inform on additional participants from these areas. We will look at other strategies, like including participants from other regions or finding additional cases through collaborating with the NTLP’s active case finding interventions, to ensure robustness of our data.

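### The hotspot definition rests on all-TB incidence although the hypothesis concerns MDR-TB, and place sharing among cases has no stated contrast

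*Protocol article*

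**What the plan says.** The Introduction of the protocol article frames hotspots by drug-resistant disease: they are areas "where MDR-TB incidence could be up to three times that of the baseline population".

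The working definition, under Objective 1, Data management and analysis, is different: "a hotspot is an area with a high TB incidence and where TB transmission happens, based on microbial genomic methods such as WGS", together with social network analysis, spatial analysis and the overlap of participants' locations on the map. The same paragraph states that "Social network analysis, in conjunction with WGS cluster data, will indicate transmission hotspots within the regions".

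The material for this comes from cases. Participant identification for Objective 1 admits "Individuals with a positive Xpert MTB/RIF result with rifampicin resistance demonstrated, and a positive" culture. Laboratory analyses sends for sequencing only "samples with proven GeneXpert MTB/RIF rifampicin resistance and shipped to Research Center Borstel (RCB) for WGS". The genomic link is at most five SNPs: "As proxy for TB cases associated with direct transmission events, a maximum pairwise genetic distance between at least two" isolates. The linked register holds TB patients. For shared spaces, "thematic analysis will be used for shared space data to identify the types of places where people with MDR-TB interact with other people".

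The Discussion confirms that the hotspots will be used to select sites for the case finding study. Hotspots are one of its three zones, each with 600 participants.

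**The concern.** Two features of the stated rule work against the study's own question.

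First, the incidence half of the definition counts all TB, while the hypothesis and the screening in Objective 2 concern MDR-TB. MDR-TB is a small fraction of TB, so an all-TB rate mostly describes drug-susceptible disease.

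Second, sequencing can show that two people are linked but not where transmission took place. The location evidence comes from the places that cases have in common. Markets, clinics or transport points that many people use will be common to cases too, and the article states no contrast that would show whether linked cases share a place more than expected.

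At stake is the choice of hotspot sites. Their yield and cost are set against those of the household and ward strategies, and feed the transmission model and the ICER. Poorly chosen sites would make the hotspot strategy look weaker than it is.

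**Working it through.** Objective 1 gives no sample size or rate calculation, so there is no figure of the plan to reproduce. Two checks follow.

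**Check 1: what an all-TB rate detects**

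Inputs, from the Introduction: MDR-TB is 4.5% of new and 7.9% of previously treated cases; about 800 MDR-TB cases a year among 12 000 TB cases, so 800/12 000 = 6.7%; national TB incidence 460/100 000. From Design: notification above 1000/100 000 in areas of Otjozondjupa.

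Let s be the MDR share of TB at baseline. Then

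all-TB ratio = s × (MDR-TB ratio) + (1 − s) × (non-MDR ratio).

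| s | MDR-TB ×3, other TB ×1: 1 + 2s | MDR-TB ×1, other TB ×3: 3 − 2s |
|---|---|---|
| 4.5% | 1.09 | 2.91 |
| 6.7% | 1.13 | 2.87 |
| 7.9% | 1.16 | 2.84 |

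The area that the hypothesis describes is hardly visible on an all-TB rate. An area with no MDR-TB excess stands out.

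The Otjozondjupa figure shows the same. 1000/460 = 2.17 times the national rate. With MDR-TB at baseline this needs non-MDR TB at (2.17 − s)/(1 − s) = 2.2 to 2.3 times baseline. With non-MDR TB at baseline it would need MDR-TB at (2.17 − (1 − s))/s = 16 to 27 times baseline. A high all-TB rate is therefore weak evidence of an MDR-TB excess.

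**Check 2: chance sharing inside a genomic cluster**

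Assumptions, not in the documents: a place is used by a share q of people, its use is unrelated to transmission, and five linked cases use it independently of one another.

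P(at least 2 of 5 name it) = 1 − (1 − q)^5 − 5q(1 − q)^4.

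| q | At least 2 of 5 | Both of a pair (q²) |
|---|---|---|
| 10% | 8% | 1% |
| 30% | 47% | 9% |
| 50% | 81% | 25% |
| 70% | 97% | 49% |

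So restricting attention to genomically linked cases does not remove the problem.

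The reason is that case data alone do not fix the association. If half of the cases use a place, their odds of use are 1. Population use of 50%, 25% or 10% (odds 1, 1/3, 1/9) then gives an odds ratio of 1, 3 or 9. Some comparison is needed to tell these apart.

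**The case against.** The strongest reply has five parts.

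- **The definition is conjunctive.** A reader might infer that an area with only drug-susceptible TB could be declared a hotspot. The documents do not support that. Transmission must also be shown, and only rifampicin-resistant isolates are sequenced, so such an area fails the genomic condition. This stands, and it narrows the error to two cases: a high-TB area with a few linked MDR-TB cases is labelled, or a true MDR-TB area misses the incidence condition.
- **Thematic analysis does not select hotspots.** A reader might infer that it does. The article gives it a descriptive role, covering contacts and types of places. This stands, and that part needs no change.
- **Counting all case pairs overstates the problem.** With 100 cases and 60% use (both assumed), 0.36 × 4950 = 1782 pairs would share a place by chance. That count ignores the rule that hotspots are tied to genomic clusters. This stands, and it is why Check 2 works within a cluster.
- **The hypothesis is not left wholly untested.** It speaks first of heterogeneity in the concentration of genotypes, which sequencing with coordinates and spatial analysis does address. The three-fold figure is an upper expectation. This stands, and it also means that a two-thirds loss of yield (1 − 1/3) at a wrongly chosen site would be an extreme.
- **A condensed article leaves detail out.** Thresholds and the spatial method may be in the full protocol or analysis plan, and their absence here is no finding. This stands, but it does not cure an incidence condition that is stated on the wrong disease.

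**Conclusion.** The concern holds in limited form. The Introduction and the Objective 1 definition use different incidence measures, and the difference is material. On the article's own shares, a three-fold MDR-TB area with baseline other TB has an all-TB ratio of 1.09 to 1.16, against 2.84 to 2.91 for an area whose excess is entirely non-MDR. This rests on the 4.5% to 7.9% range describing the MDR share at baseline, and on other TB staying at baseline in the first case.

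The second part is that place sharing is described among cases with no stated contrast. Its size depends on the assumed use of a place: 47% to 81% for 30% to 50% use and a cluster of five. Linked cases may also share places because they know one another or live close together, so independence is a simplification.

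Neither part shows that the chosen sites will be wrong. They show that the stated rule can miss the areas it seeks and can credit places that are merely busy. This should be corrected before sites are chosen.

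**What to change.** 1. **Reconcile the Introduction with the Objective 1 definition** by stating the incidence condition on MDR or rifampicin-resistant TB. Use notifications per population where denominators exist. Report them with intervals as a descriptive ranking, not as a significance requirement.
2. **Add a contrast for place sharing.** For each place or area, compare the proportion of linked pairs (at most five SNPs) that share it with the proportion among unlinked pairs from the same region. A permutation test is suitable because pairs with a case in common are not independent. Use the result as supporting evidence when choosing hotspot sites.

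The sequences, SNP distances and coordinates are already planned, so the second item costs only analysis time. The first needs local denominators. Census data appear only under Epidemiological modelling, for calibration, and small-area counts are not promised.

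State these limitations:

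- Local counts will be small. For example, 5 cases where 1.67 are expected give a ratio of 3 with an exact 95% interval of about 0.97 to 7.0, which is why significance should not be required.
- Detection is incomplete: 213 of about 800 estimated MDR-TB cases were found in 2020, so notification rates partly reflect detection.
- Some cases classed as unlinked may be linked through people who were not sampled, which would weaken the contrast.

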#### Participant identification

For the feasibility study, participants will be enrolled from three zones, namely (a) transmission hotspots, (b) household and other close contacts of MDR-TB cases identified by the TB programme, and (c) visitors to patients with MDR-TB admitted to TB wards in hospitals. A sample size calculation is not indicated since one of the goals of feasibility studies is to inform on sample size calculations for the planning of large-scale appropriately powered intervention studies.^10 11^ A sample size of 600 participants for each intervention strategy will inform on the feasibility and acceptability of the interventions, the yield and the cost per additional case.

#### Data collection

There will be both qualitative and quantitative components of this objective. For the qualitative component, pre-intervention in-depth qualitative data will be collected from three groups of participants (healthcare workers, N=~9; community members, N=~9; patients, N=~12; total N=~30) in each of the regions. A semistructured discussion guide will include discussion questions and participatory activities to elicit knowledge, beliefs and attitudes regarding MDR-TB, and acceptability of the proposed study methodology. This information will be used to inform the design and implementation of the quantitative component of the feasibility study. For the quantitative component, a scoping review on MDR-TB case finding interventions will be conducted to document case finding intervention strategies for MDR-TB in LMICs. The first intervention strategy of the feasibility study, focusing on transmission hotspots, will be tailored to the local context.^12^ For the second intervention strategy of the feasibility study, focusing on household and other contacts, MDR-TB household contact studies from Peru will be used as examples.^13 14^ Peru has a similar TB burden to Namibia, is also an LMIC and has conducted similar case finding studies which serve as good examples for this type of work; we therefore refer to the Peruvian studies as comparison. For the third intervention strategy of the feasibility study, focusing on the TB wards, all consecutive visitors of patients with MDR-TB will be asked to participate (N=~600). We are unaware of similar work of this nature and therefore cannot add comparative data for this strategy.

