#### Data management and analysis

Data from the qualitative and quantitative components of the feasibility study will be stored in separate databases. Qualitative data will be captured and analysed with ATLAS.ti using Attride-Stirling’s framework for thematic analysis to determine acceptability.^15^ Feasibility will be determined by collecting data on recruitment and retention, time required to recruit a participant, number of eligible participants required to recruit required sample size and feasibility of testing procedures and data collection methods.^16^ Yield will be determined by using a number-needed-to-screen approach for each strategy.^17^ Cost will be determined using the incremental cost-effectiveness ratio (ICER) for each case finding intervention strategy.^18^

### Objective 3

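### Acceptability is credited to the 600 participants per strategy, but the only method given for it is thematic analysis, and the only interviews described precede delivery

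*Protocol article*

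**What the plan says.** All references are to the protocol article.

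- **Abstract, Methods and analysis.** Acceptability is listed with feasibility, yield and cost as something to be examined for case finding in hotspots, in households and among hospital visitors.
- **Objective 2, Participant identification.** "A sample size of 600 participants for each intervention strategy will inform on the feasibility and acceptability of the interventions", as well as on yield and cost.
- **Objective 2, Data collection.** For the qualitative component, "pre-intervention in-depth qualitative data will be collected from three groups of participants". Their sizes in each region are "healthcare workers, N=~9; community members, N=~9; patients, N=~12; total N=~30". One discussion topic is "acceptability of the proposed study methodology". On use: "This information will be used to inform the design and implementation of the quantitative component of the feasibility study".
- **Objective 2, Data management and analysis.** The qualitative data are analysed with a "framework for thematic analysis to determine acceptability". Delivery-phase measures go to a different outcome: "Feasibility will be determined by collecting data on recruitment and retention, time required to recruit a participant", together with the "number of eligible participants required to recruit required sample size" and the feasibility of testing and data collection.
- **Objective 2, Laboratory analyses.** Participants are to have sputum and blood taken, a chest X-ray, a chest ultrasound and a rapid HIV test in the field.

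**The concern.** The article pairs each Objective 2 outcome with a method. For acceptability, the pairing does not match the sample said to inform it. The Participant identification section points to the people screened, whereas the analysis section points to qualitative data, and the only such data described come from other named groups before screening starts.

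Views on a proposal differ from the response to what is delivered. Someone may approve of household screening in an interview and later decline the blood draw or the HIV test at the door, or the reverse. The interviews also feed back into design and implementation, so what is delivered may differ from what was discussed.

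The gap matters most for ward visitors. They are not a named interview group, and the Data collection section says the team knows of no comparable work for that strategy, so outside data cannot fill it. At stake is what the acceptability result will mean to whoever plans a larger study from it.

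**Working it through.** **1. The article's own count.** Per region: 9 healthcare workers + 9 community members + 12 patients = 30, which matches the stated total. Over three regions: 30 x 3 = about 90 interviewees.

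**2. The sample said to inform acceptability.** 600 participants x 3 strategies = 1800.

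**3. The statements side by side.**

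| Question | Participant identification | Data collection, with Data management and analysis |
|---|---|---|
| Who informs acceptability? | 600 screened participants per strategy | About 30 interviewees per region, in three named groups |
| When? | During delivery | Before the intervention |
| About what? | The interventions | The proposed methodology |
| By what measure? | None given | Thematic analysis |

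The columns differ on every row. No acceptability measure is attached to the 1800, and no qualitative round is described that would reach them.

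**4. What is collected during delivery.** The analysis section names recruitment, retention, time to recruit, the number of eligible people needed to reach the sample, and the feasibility of testing procedures. The number of eligible people needed, set against the 600 recruited, comes close to an uptake proportion. It is assigned to feasibility. Acceptance of each procedure and reasons for refusal are not named.

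**5. What the screened sample could support.** For a proportion p based on n = 600, the 95% half-width is 1.96 x sqrt(p(1 - p)/n). It is largest at p = 0.5:

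1.96 x sqrt(0.25/600) = 1.96 x 0.0204 = 0.040, or 4.0 percentage points.

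This assumes simple random sampling. Contacts cluster in households and visitors cluster by patient, so the true half-width would be larger by the square root of the design effect, which the article does not give. The denominator for consent is everyone approached. That number is at least 600 if the target is met, so on the same assumption its half-width would be no wider.

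**The case against.** The strongest reply has four parts.

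*Acceptance is observed during delivery.* This stands. Recruitment, retention and the number of eligible people needed are behavioural evidence of acceptance. A reader might infer that acceptability is never measured in the people screened, or that none of the 1800 contribute to it. The document does not support that: it states that they do contribute, and it collects uptake-type data from them. The fault is that those data are assigned only to feasibility and that no acceptability measure is defined for these participants.

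*The interviews are not blind to the strategies.* This also stands. The three target zones are fixed and the methodology is already proposed, so it would be wrong to say that the interviews come before the strategies are designed. They come before the strategies are finalised and delivered. Nor does the text show that results could not be given by strategy, since the discussion guide may separate the three. The community members and patients interviewed may include contacts or visitors. The article says only that these are not named groups.

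*The article condenses a fuller protocol.* This stands in part. Refusal forms and interview schedules are commonly left to the full document, and a later qualitative round cannot be excluded. But the article itself states the timing, groups, numbers, use and method of analysis, and those statements do not fit its own sentence about the 600.

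*Formative interviews followed by tracking of uptake are a defensible arrangement.* They are, and moving interviews to after delivery would cost formative information. That argues for keeping the interviews where they are. It does not argue for reporting them as acceptability of the delivered strategies.

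A reader might also infer from the Discussion that the study fails a duty to show acceptability to communities in general. That passage concerns a future large-scale study to whose design the findings could contribute. It is not an outcome of this one.

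**Conclusion.** The point holds as an internal mismatch about the source and timing of the acceptability data. Acceptability is said to rest on 600 screened participants per strategy (1800 in all), but the only method tied to it uses qualitative data, and the only qualitative data described come from about 90 people interviewed before delivery. Followed as written, the plan yields anticipated acceptability of a proposal that the same interviews help to shape, while the uptake data from delivery count towards feasibility alone.

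This rests on reading the single qualitative round described as the one that feeds the thematic analysis. If the full protocol contains a later round or an acceptability measure for those screened, the remedy reduces to saying so. The mismatch does not affect yield or cost. It limits what can be claimed about acceptability, strategy by strategy, and is worth correcting because most of the needed data are close to what is already planned.

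**What to change.** Reconcile the three Objective 2 sections (Participant identification, Data collection, and Data management and analysis):

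1. Keep the pre-intervention interviews, label them formative, and report their result as anticipated acceptability.
2. Define acceptability of the delivered strategies on the people offered screening. Report by strategy:
   - the proportion of those approached who consent;
   - the proportion accepting each procedure (sputum, blood, X-ray, ultrasound, HIV test);
   - the reasons given for refusal.
3. State that the recruitment data already planned serve both feasibility and acceptability, and that intervals for the proportions allow for clustering within households and by patient visited.

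The cost is a short refusal log, completed when people are approached, and a little more analysis. A post-delivery interview round with household contacts and ward visitors would add depth but is optional. If it is done by re-timing planned interviews, the price is less formative information before the start.
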